#### Data Analysis

Quantitative data will first be analyzed descriptively: the recruitment, engagement, and attrition rates will be calculated; sample characteristics will be summarized (both across the total sample and within each group); and mean scores on measures will be reported (within each group). The assessment of acceptability will be based on open-ended qualitative feedback regarding impressions of the VR intervention, which will be analyzed using content analysis with NVivo 12 (Lumivero), which was designed to assist with qualitative data organization. We will also determine acceptability based on the developed Likert scale questions. Means or medians will be reported depending on the distribution of the data. A triangulation approach will be used to amalgamate data sources and comprehensively assess acceptability. Paired samples *t* tests (1-tailed) and repeated measures ANOVAs will assess whether there are changes in participant-reported symptoms across the duration of the study within the active intervention group. If power permits, independent samples *t* tests (or an ANOVA, followed by post hoc pairwise comparisons) will assess whether there are mean differences in PSA scores between (1) the active and control intervention groups and (2) the active intervention group and TAU (this will be examined descriptively if underpowered). We will also examine changes in physiological arousal (an objective indicator of distress), assessed via skin conductance and heart rate, between and within (ie, during VR intervention vs within OR) intervention groups, and we will assess whether self-reported distress and anxiety scores are correlated with the indices of physiological arousal. Physiological data will also be integrated in the VR technological paper (in development) to understand whether physiological indices change during the VR experience (indicative of immersion). Finally, if power permits, independent samples *t* tests and ANOVAs will assess whether there are mean differences in patient-reported symptoms according to certain sample characteristics (eg, age, clinically significant anxiety, history of previous surgery, and type of surgery), both within the active intervention group and within the complete sample.

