
On the day of surgery, all participants are asked to complete the PITI, the APAIS, and the NCCN Distress and Anxiety Thermometer either while they are in the waiting room or in the preoperative holding area (depending on when is most convenient and the timings of surgeries). Furthermore, we again monitor participants’ skin conductance and heart rate at this time. Participants are also asked to provide an additional rating for the NCCN Distress or Anxiety Thermometer while in the OR; instead of using the paper copy in the OR, the study coordinator or anesthesiologist asks participants to verbally indicate their current level of distress and anxiety (ie, on a scale ranging from 0 to 10). Five days after surgery, participants are asked to complete the NCCN Distress and Anxiety Thermometers; the PROMIS anxiety, depression, global health, fatigue, and pain intensity scales; a visual analog anxiety and distress graph; a postoperative summary form (to capture length of hospital stay and impressions of the various preoperative anxiety and distress measures); the BRCS; and the Peritraumatic Distress Inventory. Those in the active intervention group also receive open-ended questions requesting feedback to inform modifications that should be made to the second model of the simulation (in phase 3). Finally, 30 days after surgery, participants are asked to complete the NCCN Distress and Anxiety Thermometers; the PROMIS anxiety, depression, global health, fatigue, and pain intensity scales; the BRCS; and the Primary Care Screen for Posttraumatic Stress Disorder Diagnostic and Statistical Manual of Mental Disorders, Fifth Edition.

As will be detailed in the feasibility manuscript, although a number of self-report and objective measurements were obtained, the primary measures relate to feasibility (eg, recruitment and dropout rate as well as VR impressions and feedback). This feasibility study will also evaluate the extent to which these measures are completed as instructed and best represent PSA and whether preliminary trends support decreases in PSA across the study duration. The primary outcome measure for the larger future clinical trial will be determined based on this study. The proposed primary outcome measures of interest include the PITI, the APAIS, and the NCCN Distress and Anxiety Thermometers.

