Although feasibility and pilot studies are critical in the development of new interventions, the generalizability of the findings is limited. Therefore, when published, the results of the feasibility trial will need to be interpreted with caution. Relatedly, the focus of these 3 initial phases has been on patients undergoing oncological surgery, namely patients undergoing breast cancer surgery, which may differ in important ways from other noncancer surgical samples. In addition, within the VR program itself, there was 1 variation of the patient avatar, and it does not reflect differences in gender, body type, or ethnicity, which may potentially decrease patient embodiment within the VR intervention and the ecological validity on the day of surgery. Furthermore, we did not ask background questions related to ethnicity, sexual orientation, or disability and, therefore, are limited in understanding feasibility aspects across diverse populations. The sample size is also underpowered to reliably detect effects but will be able to inform future RCTs in terms of design and implementation. Furthermore, preliminary trends in the data will increase confidence in the potential utility of the intervention. Relatedly, the exclusion of the VR control group (ie, non-OR VR) as per our amendment limits our ability to understand preliminary effects of the VR intervention. It is possible that any anxiety-reduction trends for the VR intervention group compared to TAU may relate to a factor other than the effect of the intervention itself (eg, an additional appointment before surgery and the opportunity to discuss fears). It will be particularly important for future RCTs to include a comparable comparison group to elucidate potential mechanisms. A future RCT is planned to test the final iteration of the VR OR, and we intend to compare it to a mobile phone–based intervention using the same components of the simulation as well as TAU. This will allow us to disentangle the potential additive effect of immersion that exists only in VR applications. Finally, recent research by our group [72] and others demonstrates that PSA for oncological surgery relates to a range of factors, including uncertainty of the health trajectory, recovery [79,80], and the psychosocial implications of surgery. Our prototype intervention only targets 1 component of PSA (ie, exposure to the OR and information regarding induction), which may not result in meaningful reductions among those with PSA related to other factors. However, the results from these 3 phases will allow us to refine the VR intervention to best meet patients’ needs and integrate all possible features to further ameliorate PSA (eg, relaxation strategies). Future versions of the simulation may also include advanced VR features, such as relevant haptic feedback, as the technology develops further.

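### The only unconditional tests of anxiety change are uncontrolled pre-post tests in the active arm; the randomised VR-versus-TAU difference should be the estimate that is always reported

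*Protocol article*

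**What the plan says.** All of the following is in the protocol article.

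- **Within the active arm, no condition (Data Analysis).** Paired t "tests (1-tailed) and repeated measures ANOVAs will assess whether there are changes in participant-reported symptoms". Their scope is fixed by the words that follow: "across the duration of the study within the active intervention group". The t tests are 1-tailed; no direction is given for the ANOVAs.
- **Between arms, conditional (Data Analysis).** If there is enough power, t tests or an ANOVA "will assess whether there are mean differences in PSA scores between (1) the active and control intervention groups and (2) the active intervention group and" one further arm, which is TAU. Otherwise "this will be examined descriptively if underpowered". The article gives no threshold for enough power.
- **Reported in any case (Data Analysis).** "mean scores on measures will be reported (within each group".
- **Power (Limitations).** "The sample size is also underpowered to reliably detect effects". The same section adds that "preliminary trends in the data will increase confidence in the potential utility of the intervention".
- **Use of trends (Measures).** The study will evaluate "whether preliminary trends support decreases in PSA across the study duration", and the primary outcome of the later trial will be settled from this study.
- **Timing (Protocol subsection).** All participants, TAU included, report about 2 weeks before surgery, on the day of surgery, and 5 and 30 days after it.
- **Arms (Results).** The VR control arm was dropped, which leaves VR versus TAU.

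**The concern.** The section headed PSA Risk and Defining Features calls preoperative state anxiety transient and driven by a current stressor such as upcoming surgery. A score of this kind moves over the weeks around an operation whether or not the patient has used VR, so a pre-post change in one arm is VR effect plus natural course. That uncontrolled change is what the plan commits to testing. The randomised contrast, which removes natural course, gets a test only under a condition that the article's own power statement suggests will not be met.

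The 1-tailed t test adds a second weakness: it cannot show worsening. Yet the acceptability questionnaire asks participants whether VR made their anxiety or concerns worse.

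At stake is how preliminary utility is judged on the way to a larger trial. The p-values produced would be ones that cannot be attributed to VR, while the attributable comparison might appear only as two columns of means with no statement of uncertainty.

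**Working it through.** **The plan's own figure.** The target is 45 = 3 × 15, which agrees. It rests on feasibility guidelines and earlier studies. No alpha, power, effect size or SD is stated, so there is no power calculation to reproduce.

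**Inputs from the article.** 15 per arm as planned; 8 recruited from December 2021 to December 2022 and 15 more from January to September 2023, so 8 + 15 = 23 by then.

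**Assumptions, not in the article.** Alpha 0.05; the standardised shifts below; a near-equal 12/11 split of the 23 between VR and TAU (the article does not give the split); a baseline-to-outcome correlation r of 0.5 or 0.7.

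**Step 1. The 1-tailed paired test when VR does nothing.** Let dz be the natural fall divided by the SD of the change score. The test statistic is noncentral t with n − 1 degrees of freedom and noncentrality dz × √n. At n = 15 the critical value is 1.761; for dz = 0.5 the noncentrality is 0.5 × √15 = 1.94.

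| Natural change (dz) | Significant, n = 15 | Significant, n = 12 |
|---|---|---|
| fall of 0.2 | 18% | 16% |
| fall of 0.3 | 30% | 25% |
| fall of 0.5 | 58% | 49% |
| fall of 0.8 | 90% | 83% |
| none | 5% | 5% |
| rise of 0.3 | 0.3% | 0.4% |

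Making the test two-sided does not cure this: at n = 15 and dz = 0.5 it is still significant in 44% of trials. The main problem is the missing comparator; the sidedness is secondary.

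**Step 2. A real benefit against a rising background.** Suppose anxiety would rise by 0.5 SD of change towards surgery and VR takes off 0.5. The net change is 0 and the test is significant in 5% of trials, its error rate. If the rise is 0.8 and VR takes off 0.5, the net change is a rise of 0.3 and the figure at n = 15 is 0.3%. A benefit that only blunts the rise is invisible to this test.

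**Step 3. Can the power condition be met?** For a two-sample t test, two-sided 0.05, the noncentrality is d × √(n1·n2/(n1 + n2)).

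| | 15/15 | 12/11 |
|---|---|---|
| Power at d = 0.5 | 26% | 21% |
| Power at d = 0.8 | 56% | 45% |
| d needed for 80% power | 1.06 | 1.23 |

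By normal approximation, 80% power needs 63 per arm for d = 0.5 and 25 per arm for d = 0.8. On any usual reading the condition fails.

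**Step 4. What the randomised estimate can deliver.** Unadjusted half-width of the 95% CI, in SD of the score: t × √(1/n1 + 1/n2).

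- 15/15: 2.048 × 0.365 = 0.75.
- 12/11: 2.080 × 0.417 = 0.87.

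Adjusting for baseline multiplies the standard error by √(1 − r²) and costs one degree of freedom.

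- 15/15, r = 0.5: 2.052 × 0.365 × 0.866 = 0.65.
- 15/15, r = 0.7: 2.052 × 0.365 × 0.714 = 0.53 to 0.54.
- 12/11, r = 0.5: 2.086 × 0.417 × 0.866 = 0.75.

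These intervals are wide, but unlike the within-arm p-value they estimate the effect of being offered VR rather than TAU.

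**The case against.** The other side has a good deal of force.

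- **The randomised comparison is not abandoned.** If underpowered it is examined descriptively, and group means are reported regardless. A reader might infer that the trial itself cannot separate VR from natural course, or that the randomisation goes unused. The article does not support that: TAU is concurrent, randomised and measured at the same times. This stands, and it confines the point to the planned inference.
- **Worsening is not hidden.** A reader might infer from the 1-tailed test that harm could not be shown. The repeated measures ANOVAs are non-directional, and the group means, the ratings and behavioural observation during VR, and the acceptability item can all show worsening. Only the t test cannot. This stands too.
- **The trends are not said to be within-arm.** The Limitations section speaks of trends in the data generally, asks for caution, and warns that a VR-versus-TAU trend may reflect something other than the intervention. Nowhere does it say that a fall after surgery will be credited to VR. But that warning concerns the between-arm contrast; natural course in the pre-post tests is not mentioned.
- **The direction of natural change is unknown.** The 58% rests on an assumed fall. In the Measures section, PITI and APAIS are not listed after the day of surgery (the Protocol subsection has the PSA measures repeated on day 5), so for those scales the contrast may run only up to surgery, where a rise is plausible and the 1-tailed test is conservative. That removes the false-positive worry for those scales and leaves the missed benefit of Step 2.
- **Utility is secondary and preliminary, and low power is admitted.** This stands and limits severity. It does not explain why the uncontrolled change gets the unconditional test. An undefined power threshold alone would be a detail for a fuller plan; the ordering of the two analyses is stated in the article.

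**Conclusion.** The point holds in this form: the only unconditional tests of self-reported symptom change have no comparator, and the paired t tests among them are 1-tailed, while the randomised test hangs on a condition that the article in effect concedes is unmet. Those p-values cannot distinguish a VR effect from the course of a state the article calls transient. With no VR effect at n = 15, the 1-tailed test is significant in 18% to 90% of trials for assumed natural falls of 0.2 to 0.8 SD of change (58% at 0.5). Against a rising background it misses a benefit that only blunts the rise. These shifts, alpha and the correlations are assumptions; the article supplies none of them.

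Severity is moderate. No efficacy decision rule rests on these tests, feasibility is the primary purpose, and the data needed for a better analysis are already collected.

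**What to change.** 1. Remove the power condition on the VR-versus-TAU comparison. Always report the VR-minus-TAU difference in day-of-surgery score for PITI, APAIS and the distress and anxiety thermometers, each with a two-sided 95% CI, from a linear model with arm and the baseline score taken before VR exposure. State which of the two day-of-surgery thermometer readings (waiting or holding area, or operating room) is used.
2. Show the unadjusted difference beside it, because participants are randomised at the recruitment call and so give the baseline score after allocation, at the visit for VR and by mail or web for TAU.
3. Keep within-arm change descriptive, with means and intervals for both arms. If the within-arm tests are retained, make them two-sided and say that they do not estimate an effect of VR.
4. Base any statement about preliminary utility on the between-arm estimate and its interval, and reword the Limitations sentence on trends to match.

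Adding the stratification factors, or an arm-by-time mixed model for later visits, is optional at about 23 participants.

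The cost is a change of analysis wording and no new data. The downside is that results appear as wide intervals, roughly 0.65 to 0.87 SD either side over the two sample sizes, unadjusted or with r = 0.5, in place of p-values.

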#### Protocol

Phase 2 used a single-blind randomized design (1:1:1 randomization; stratified according to surgery type [with vs without reconstruction] and whether neoadjuvant chemotherapy was received; stratification enables equal proportions of participants with these characteristics across each of the 3 study groups), using quantitative and qualitative methodologies. This was done to assess the feasibility of, and pilot-test, the VR simulation to expose patients undergoing breast cancer surgery to the OR and induction process (ie, VR OR) compared to a non–surgery-related VR simulation (ie, VR control) and TAU. All participants complete self-report measures approximately 2 weeks before surgery (ie, baseline; for VR groups, this will occur on the day of the VR visit as well as before and after testing the intervention), on the day of surgery (preoperative period), 5 days after surgery (acute postoperative period), and 30 days after surgery (30-day postoperative follow-up).

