Randomization is carried out using a web-based random number generator (details of how these random numbers are generated are available on the website) [60]. A master file was created in Excel (Microsoft Corp) by author JS, which consisted of 4 different stratification groups to correspond to the number of possible combinations: no chemotherapy and no reconstruction; no chemotherapy, with reconstruction; chemotherapy, no reconstruction; and chemotherapy and reconstruction. Using the web-based number generator, each stratification group was populated with equal proportions of the randomly ordered numbers (1, 2, or 3) that corresponded to the intervention groups to which a participant could be assigned (1: OR intervention; 2: Nature Treks VR intervention, and 3: TAU). Only research personnel who randomized the participants had access to the file. Due to the nature of this study, only partial blinding was possible. Specifically, those in the TAU group received no VR intervention, but those randomized to VR control versus the VR active intervention were blinded. Participants randomized to either the active intervention or VR control group schedule a meeting date to undergo the VR intervention, approximately 2 weeks before their surgery, during their telephone call with the study coordinator. On the day of the intervention meeting, participants complete baseline questionnaires before the intervention and additional questionnaires after the intervention (detailed in the *Measures* section). Those randomized to TAU are either emailed a link to complete the baseline measures using Qualtrics software (Qualtrics International Inc) or are mailed a hard copy, depending on their preference, 2 weeks before their surgery (baseline). On the day of surgery (preoperative period), participants again complete the measures assessing PSA that had been assessed at baseline. Five days after surgery (acute postoperative period), participants will complete the PSA measures, in addition to the other initial baseline measures. Finally, all baseline measures are readministered at the 30-day postoperative follow-up. For both postoperative follow-ups, participants have the option to receive hard copies of the measures via mail (to complete within 72 hours) or a survey link to complete the measures on the web.

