#### Measures

A variety of self-report measures are administered to participants across 4 time points of this study (ie, baseline or VR visit, preoperative period, acute postoperative period, and 30-day postoperative follow-up). Baseline measures are administered approximately 2 weeks before surgery (at the VR intervention visit for the intervention groups or via mail or web-based for the TAU group). These measures include a background sociodemographic questionnaire (eg, assessing age, marital status, diagnosis, type of surgery, previous history of surgeries, and mental health diagnoses); the Preoperative Intrusive Thoughts Inventory (PITI) [61]; the Amsterdam Preoperative Anxiety Information Scale (APAIS) [62]; the NCCN Distress Thermometer (a visual analog scale; also adapted for anxiety) [63,64]; the Peritraumatic Distress Inventory [65]; the Primary Care Screen for Posttraumatic Stress Disorder Diagnostic and Statistical Manual of Mental Disorders, Fifth Edition [66]; the Brief Resilient Coping Scale (BRCS) [67]; and the Patient-Reported Outcomes Measurement Information System (PROMIS) anxiety [68], depression [68], global health [69], fatigue [70], and emotional support scales [71]. The sociodemographic data collected were informed by the methodology used in a previous study by Grocott et al [72] that itself informed the current methodological approach. All mental health symptom scales are empirically validated self-report measures in various health populations, languages, and cultures. During the VR simulation, we also monitor participants’ skin conductance (using eSense Skin Response [Mindfield Biosystems Ltd]) and heart rate (using a Fitbit device [Google LLC]) while engaged in the VR simulation; participants are asked to report their level of distress and anxiety (using the NCCN Distress and Anxiety Thermometer scale ranging from 0 to 10) during the intervention (approximately 7 min from the start time). Throughout the simulation, research personnel complete a standardized behavioral observation form recording any notable verbal or nonverbal indications while in the intervention. After the simulation, the intervention groups complete the Igroup Presence Questionnaire [73] and a patient acceptability questionnaire (developed by the research team and including both closed-ended and open-ended items for participants to describe their impressions of the intervention). The patient acceptability questionnaire contains questions pertaining to rating the extent (on a scale ranging from 0% to 100%) to which the participant agrees to 13 statements about the VR intervention (eg, “I found the VR intervention was helpful” and “The VR intervention worsened my anxiety/concerns about my surgery”), open-ended and closed-ended questions about motion sickness, open-ended questions about what the participant liked and disliked and what they found helpful about the VR (if applicable), open-ended and closed-ended questions about whether the VR intervention was worthwhile, and a closed-ended question about other elements that should be included in the VR OR simulation.

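### The repeated measures ANOVA named for change over time is by default a complete-case test on scales with three or more visits; a mixed model would keep partly observed participants

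*Protocol article*

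**What the plan says.** The Data Analysis section names two methods in one sentence for symptom change in the active arm: 1-tailed paired t tests, and a second method described as "repeated measures ANOVAs will assess whether there are changes in participant-reported symptoms across the duration of the study within the active intervention group". The same section also promises attrition rates and mean scores within each group.

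On data collection, the Measures section states that "A variety of self-report measures are administered to participants across 4 time points of this study". After baseline, the Protocol section places these "on the day of surgery (preoperative period), 5 days after surgery (acute postoperative period), and 30 days after surgery (30-day postoperative follow-up". The two postoperative sets are returned by mail or web link; the day-of-surgery set is completed on site.

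The scales differ by visit, and the article gives two accounts:
- Measures section: "On the day of surgery, all participants are asked to complete the PITI, the APAIS, and the NCCN Distress and Anxiety Thermometer". The PITI and APAIS are not listed at day 5. For day 30 the list begins "Finally, 30 days after surgery, participants are asked to complete the NCCN Distress and Anxiety Thermometers" and again omits the PITI and APAIS.
- Protocol section: the PSA measures are completed at day 5 along with the other baseline measures. Then: "Finally, all baseline measures are readministered at the 30-day postoperative follow-up".

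On status, the Measures section says that "the primary measures relate to feasibility (eg, recruitment and dropout rate as well as VR impressions and feedback". Symptom change is treated as a preliminary trend.

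**The concern.** Classical repeated measures ANOVA works on one complete row per participant. Someone who gave the baseline and day-of-surgery thermometer ratings but did not return the day-5 or day-30 form contributes nothing to it, although the preoperative ratings are the ones closest to the target of the intervention. The paired t tests and the ANOVA would then describe different sets of people.

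This trial makes dropout a primary measure and assesses whether forms are completed as instructed. It therefore treats incomplete data as a live question while naming a method that does not tolerate them, in an arm of about 15 or fewer. At stake are the precision of the longitudinal test and its assumption about missingness. The result has some use: the Limitations section says preliminary trends will raise confidence in the intervention, and the Measures section says the future trial's primary outcome will be chosen from this study.

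**Working it through.** **Inputs from the article.** The Overview of Phase 2 plans 45 participants in three arms: 45 / 3 = 15 per arm, which reproduces the stated figure. The Limitations section reports 8 + 15 = 23 recruited by September 2023. The Results section says the VR control arm was dropped and recruitment ran to December 2023. No attrition rate, alpha, SD or final arm size is given.

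**Visits per scale.**

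| Scale | Measures section | Protocol section |
|---|---|---|
| Thermometers | 4 | 4 |
| PITI, APAIS | 2 | 4 |
| PROMIS anxiety, depression, global health, fatigue | 3 | 3 |

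With two visits, repeated measures ANOVA reduces to a paired t test, so the issue arises only with three or more.

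**Complete cases.** Assume baseline is present and each of k follow-ups is missed independently with probability m. Expected complete cases = n(1 − m)^k. An analysis of all available visits keeps a share (1 + 3(1 − m)) / 4 of the observations on a four-visit scale. For n = 15:

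| m | k = 3 (thermometers) | k = 2 | k = 1 | Observations kept, four-visit scale |
|---|---|---|---|---|
| 5% | 12.9 (86%) | 13.5 | 14.25 | 96% |
| 10% | 10.9 (73%) | 12.2 | 13.5 | 92.5% |
| 20% | 7.7 (51%) | 9.6 | 12.0 | 85% |

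The k = 2 column covers the three-visit PROMIS scales. It also covers the thermometers if loss occurs only at the two remote follow-ups. The k = 1 column also shows what remains if the same people miss every follow-up: 15 × 0.90 = 13.5 at 10%.

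If the active arm held half of the 23 recruited by September 2023 (assumption: 11.5), k = 3 gives 11.5 × 0.729 = 8.4 at 10% and 11.5 × 0.512 = 5.9 at 20%. The true arm could be larger, since recruitment continued, or smaller, since a third arm existed earlier.

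**Direction of bias.** This was illustrated by simulating four visits with correlation 0.6, a true mean of zero throughout, and a logistic chance of dropout at each follow-up depending on the previous score (intercept −2.2; slope 0, 0.5 or 1.0). All settings are assumed.
- Slope 0: 73% complete, no bias.
- Slope 0.5: 71% complete; completer means 0.09 to 0.12 SD too low; baseline-to-last change off by +0.02 SD.
- Slope 1.0: 67% complete; completer means 0.19 to 0.24 SD too low; change off by +0.045 SD.

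In this illustration, completer symptom levels are understated, while the estimated change is hardly affected.

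**The case against.** The strongest reply has four parts.

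1. **The article does not say that incomplete participants will be deleted.** A rule such as imputation could sit in a full protocol or SAP that is not shown. This stands: silence on missing data is not the point. What remains is that the article names a method whose default is complete-case.
2. **The rest of the analysis is not restricted to completers.** This stands. A reader might infer that the whole symptom course, and the pilot means and SDs, will be those of completers. The documents do not support that: a paired t test loses a participant only when one of its two visits is missing, and the group means are reported separately and are not tied to complete rows.
3. **The size is assumed.** This stands. Independent loss at all three follow-ups is the harsher pattern; the day-of-surgery forms are completed on site, and withdrawals tend to cluster in the same people.
4. **The analysis is within one arm, secondary and declared underpowered.** This limits the consequence. No decision rule rests on it.

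A reader might also infer that the ANOVA will overstate recovery because patients who feel worse do not return forms. Nothing in the article supports that direction. In the illustration above the error in change was small and did not favour recovery. If nonresponse depends on how the patient feels at the missed visit, the mixed model would not correct it either.

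**Conclusion.** The point holds in a limited form. On scales with three or more visits, the named ANOVA is by default a complete-case test, and a participant who misses one visit is lost to it. This covers the thermometers and the repeated PROMIS scales, and the PITI and APAIS only if the Protocol section is the correct account. Under assumed independent loss of 5% to 20% at each of three follow-ups, about 13 to 8 of 15 participants would remain for the thermometers; milder patterns leave more. The consequence is modest, because this is a preliminary analysis in a feasibility trial. It is still worth changing, since a better method is available at almost no cost.

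**What to change.** - For scales with three or more visits, replace the repeated measures ANOVA with a linear mixed model using every available observation: categorical time, random participant intercept, REML, and a small-sample degrees-of-freedom correction.
- Report the number analysed for each scale and visit.
- Compare preoperative scores of participants with and without later follow-up.
- Reconcile the Protocol and Measures sections on which scales are collected at day 5 and day 30, because this determines which scales the change covers.

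The cost is a change of wording and slightly different code, with no new data; the article reports that analysis was still under way. The gain is retained data and validity under missing at random rather than missing completely at random. The remaining limit is that bias persists if nonresponse depends on unobserved scores, and the report should say so.
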